3. OBJECTIVES

3.1. Primary objective:

To evaluate the effectiveness of a new cervical device called DUDA in preventing late cervical canal stenosis in women undergoing conization with a high-frequency scalpel.

3.2. Secondary objectives:

3.2.1. Assess the safety of using the device;

3.2.2. Compare the quality of life in women with and without the device after surgery;

3.2.3. Compare the rate of visualization of the squamous-columnar junction (JEC) in women who used the device or not (3 and 6 months after surgery);

3.2.4. Describe menstrual periods in women who used device placement after surgery.

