Endocervical canal stenosis (early and late) will be assessed through clinical information and physical examination at each visit to the hospital after surgery. The participant will be asked about menstrual flow and dysmenorrhea during anamnesis, which would indirectly show whether the endocervical canal is patent or not. In the physical examination, after viewing the cervix through specular examination, the doctor will check the permeability of the canal by introducing the hysterometer through the cervical canal. The difficulty of introducing the 2.5mm hysterometer through the channel will be noted according to the following scale:

The possible passage of the hysterometer?

( ) No difficulty

( ) Little / Moderate difficulty, however possible passage of the hysterometer

( ) Could not pass

4.10.3. Quality of life:

Quality of life questionnaires are used in clinical trials and include important outcomes such as postoperative pain and related symptoms. For these assessments, in the present study, the following instruments will be used:

a) Functional Assessment of Cancer Therapy - Cervix Cancer (FACT-Cx), version 4.0, in Portuguese (Annex 1).

b) Universal Pain Assessment Tools: comprises the Visual Analog Pain Scale (VAS), the Numeric Visual Pain Scale (EVN) and the Faces Pain Scale (EF) (Annex 2).

4.11. Study interruption rules:

Below are the study interruption criteria:

a) Registration of a single grade 5 adverse event at any stage of the study;

b) Record of two grade 3 or 4 adverse events in the first stage of the study;

c) Record of two grade 3 or 4 adverse events in the second stage of the study;

d) the benefit of using the device under interim analysis;

e) Identification of considerable risk to participants not provided in this research protocol.

In any of the aforementioned situations, the researcher, before interrupting the study, will communicate the Research Ethics Committee (CEP) of the Barretos Cancer Hospital and await the substantiated opinion, unless the risk to the participants is imminent. In the latter situation, the researcher will interrupt the study to safeguard the research participants and will communicate the CEP as soon as possible.

4.12. Study visits and data collection:

TABLE 1 summarizes the activities carried out in the study according to the time of the visits.

4.12.1. Baseline visit:

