At the time of the initial visit, preoperative tests (blood count, serum biochemistry, coagulogram, chest X-ray, electrocardiogram and pregnancy test) and pre-anesthetic evaluation of women in whom CAF is indicated will be checked. This preoperative assessment is done on a routine basis and does not include specific aspects of the study. Women who are eligible for CAF and meet the study's eligibility criteria will be invited to participate in the survey. Those who agree will sign the Informed Consent Form at the initial visit.

During this visit, demographic and clinical information will be collected through interviews and consultation of medical records (Annexes 3). At this time, the quality of life questionnaires will also be applied.

4.12.2. Operative and postoperative visits:

On the day of surgery, a form will be filled out with the data pertinent to the surgical procedure. (Annex 4).

Postoperative visits will take place 15 days (1-PO) and 30 days (2-PO) after surgery. (Annexes 5 and 6). The acceptable windows of opportunity for visits will be ± 3 days. During these visits, the participants will undergo a medical consultation, when anamnesis and gynecological physical examination will be carried out. They will also answer the quality of life questionnaires. Any adverse event will be recorded on a specific form each post-operative visit in accordance with the Common Terminology Criteria for Adverse Events v3.0 (CTCAE V3). (Annex 7).

Participants who have the DUDA device will have it removed during the 2-PO visit during the gynecological examination.

4.12.3. Follow-up visits:

Follow-up visits will take place 3, 6, 12 and 18 months after surgery (respectively FUP-1, FUP-2, FUP-3 and FUP-4) according to our flow chart described below. The acceptable windows of opportunity for visits will be ± 10 days. During these visits, participants will undergo a medical consultation, when anamnesis and gynecological physical examination will be performed, which will include the collection of material for cervical cytology, hysterometry to assess the permeability of the endocervical canal and colposcopy to visualize the squamocolumnar junction. The degree of permeability of the channel will be recorded in a specific form. During follow-up visits, quality of life questionnaires will also be applied and adverse events will be recorded and follow-up information will be collected (Annex 8-11).

4.12.4. Surgery information:

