5. SAMPLE CALCULATION

5.1. First step:

For the safety analysis of the device, 25 women will be included, as advised by the National Ethics and Research Commission (CONEP).

5.2. Second stage:

The sample calculation assumed the premise of a cervical canal stenosis rate of approximately 15% to 20% after the CAF described in the literature and reduced to 6% with the use of an endocervical device according to the uncontrolled trial by Luesley et al (11) Considering this difference in stenosis rates (15-20% vs. 6%), an alpha error of 5%, a beta error of 20% and a balanced allocation 1: 1, the sample estimate ranges from 104 to 203 in each group. Therefore, this stage of the study will recruit 120 women in each arm, totaling 240 participants.

It is estimated that recruitment will take place between 1 to 3 weeks in the first stage and between

25 to 30 weeks in the second stage, since the potential for recruitment is 06 to 10 surgeries per week.

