6. STATISTICAL ANALYSIS

The casuistry will be characterized by means of descriptive statistics. Quantitative variables will be described by means and standard deviation or median and 25-75 percentiles, depending on their distribution. Qualitative variables will be described using absolute and relative frequencies.

The rates of stenosis of the cervical canal will be compared between the groups at different times of observation from the moment 2-PO using the chi-square test or Fisher's exact test, depending on the values ​​observed in the contingency tables. Adverse events are characterized by means of absolute and relative frequencies, and inferences are made using a 95% confidence interval. The calculation of the scores of the domains of the FACT-Cx questionnaire will follow the guidelines of the manual of the organization FACIT (Functional Assessment of Chronic Illness Therapy). The scores will be compared between the groups at each moment of observation using the t-test or Mann-Whitney test, depending on the data distribution. In all statistical calculations, the level of significance considered will be 5%.

An interim analysis is foreseen in the transition from the first to the second stage of the study and when the casuistry of the second stage reaches 25%, 50% and 75% of the recruitment estimate.

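### FACT-Cx scores are compared between arms visit by visit without using the scheduled baseline score, which gives up precision on a secondary objective

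*Protocol*

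**What the plan says.** The second secondary objective (Protocol, Section 3.2.2) is to "Compare the quality of life in women with and without the device after surgery". Section 4.10.3 names the FACT-Cx questionnaire and a set of pain scales as the instruments.

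On timing, Section 4.12.1 says of the initial visit, which precedes surgery: "At this time, the quality of life questionnaires will also be applied". Sections 4.12.2 and 4.12.3 repeat the questionnaires at 15 and 30 days and at 3, 6, 12 and 18 months. The activity table in Section 4.12.4 marks quality of life at all of these and also on the day of surgery.

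On analysis, Section 6 scores the FACT-Cx domains by the questionnaire organisation's manual and then states: "The scores will be compared between the groups at each moment of observation using the t-test or Mann-Whitney test, depending on the data distribution". The significance level is 5% throughout. Neither that section nor any other mentions a baseline covariate, a change score or a repeated-measures model.

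**The concern.** The baseline score is the one pre-randomised-treatment measurement of the same quantity that is later compared, so it is the natural covariate. Here it is scheduled for everyone and then left out of the comparison. This is not a detail left for a later analysis plan. The protocol names the test, and the named test is unadjusted.

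What is at stake is how sharply the trial can describe the effect of the device on quality of life, including the roughly 30 days it is in place. The sample size was set on stenosis alone (Section 5.2), so precision for FACT-Cx is whatever 120 women per arm happen to give. An analysis that ignores baseline gives wider intervals and a larger smallest detectable difference than the same data could support.

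**Working it through.** **1. The plan's own figure.** The only sample-size figure is for stenosis (Section 5.2): 15% to 20% in controls against 6% with the device, with "an alpha error of 5%, a beta error of 20% and a balanced allocation 1: 1", giving 104 to 203 per group. The two-sided two-proportion formula is n₀ = [1.96·√(2p̄q̄) + 0.8416·√(p₁q₁ + p₂q₂)]² / d², with continuity correction n = (n₀/4)·[1 + √(1 + 4/(n₀d))]².

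- 20% v 6%: d = 0.14, n₀ = 90 after rounding up, corrected n = 104.
- 15% v 6%: d = 0.09, n₀ = 181 after rounding up, corrected n = 203.

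Both ends reproduce exactly. The protocol then settles on 120 per arm: "this stage of the study will recruit 120 women in each arm, totaling 240 participants". It gives no standard deviation, target difference, power or baseline correlation for FACT-Cx, so there is no stated quality-of-life figure to reproduce.

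**2. Precision of the planned test.** Inputs: n = 120 per arm, two-sided 5%, 80% power, no dropout, differences in units of the score's standard deviation (SD = 1).

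- Standard error of the arm difference: √(2/120) = 0.129.
- 95% CI half-width: 1.96 × 0.129 = 0.253 SD.
- Detectable difference: (1.96 + 0.8416) × 0.129 = 0.362 SD.

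**3. Precision with baseline adjustment.** ANCOVA on the baseline score multiplies the variance by 1 − ρ². CI half-width and detectable difference scale by √(1 − ρ²). The equivalent unadjusted total is 240/(1 − ρ²). The values of ρ are assumptions.

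| ρ | Variance factor | CI half-width (SD) | Detectable difference (SD) | Power at 0.362 SD | Equivalent total N |
|---|---|---|---|---|---|
| 0 | 1.00 | 0.253 | 0.362 | 80.0% | 240 |
| 0.3 | 0.91 | 0.241 | 0.345 | 83.6% | 240/0.91 = 264 |
| 0.5 | 0.75 | 0.219 | 0.313 | 89.9% | 240/0.75 = 320 |
| 0.7 | 0.51 | 0.181 | 0.258 | 97.5% | 240/0.51 = 471 |

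**4. Check by simulation** (120 per arm, 4,000 runs per ρ, normal scores). At a true difference of 0.362 SD, the unadjusted t-test had power of 79% to 80%. ANCOVA had about 83%, 90% and 98% at ρ = 0.3, 0.5 and 0.7. With no true difference, rejection rates were 4.6% to 5.4% for the t-test and 4.7% to 5.0% for ANCOVA. Both are valid, and the adjusted analysis is sharper.

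These figures compare means. Where the plan would switch to Mann-Whitney they indicate the size of the loss and are not exact.

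**The case against.** The strongest reply is that nothing here is an error. The t-test and the Mann-Whitney test are conventional, keep their level under 1:1 randomisation, and serve a secondary endpoint. A separate analysis plan, if one exists, might adjust for baseline. The size of the gain depends on a correlation the documents do not give, and a single preoperative score may predict poorly 18 months after surgery. All of this stands except that the matter can be left to another document: the protocol states the unadjusted test outright, so an adjusted analysis would depart from it.

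Several stronger readings are tempting and should not be drawn.

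- *The tests are biased by chance baseline imbalance.* They are not. That imbalance is already reflected in the unadjusted standard error, so it is the same loss of precision and not a second harm.
- *Repeated testing will produce false findings.* Under the null, the chance of at least one is 1 − 0.95⁷ = 30% for seven independent tests and 1 − 0.95⁸ = 34% for eight. Scores from the same women are normally positively correlated, which lowers both figures. Baseline adjustment does not address multiplicity in any case.
- *The plan tests for a difference at baseline.* Section 6 can be read that way, but Section 3.2.2 limits the comparison to the period after surgery. The protocol never says that a baseline test will be run.
- *There are seven later assessments.* That count comes from the activity table. The text of Sections 4.12.2 and 4.12.3 describes six, and for the day of surgery mentions only a surgical form.

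**Conclusion.** The point holds as one of efficiency. Section 6 prescribes an unadjusted comparison while a scheduled baseline score goes unused. The planned tests are valid but less precise than the same data allow.

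The variance given up is ρ²: 9%, 25% or 49% at ρ = 0.3, 0.5 or 0.7, equivalent to about 264, 320 or 470 women instead of 240. This rests on three assumptions: the values of ρ, near-complete baseline questionnaires, and no dropout. If the correlation fades by 12 to 18 months the gain at those visits shrinks, and at ρ = 0 there is none.

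A reader might infer that the quality-of-life results would be unreliable or the trial's conclusion weakened. The documents do not support that: the stenosis comparison and the sample size do not depend on this sentence. It should be changed because the improvement is nearly free.

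**What to change.** Replace the FACT-Cx comparison sentence in Section 6 with one that specifies:

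- a between-arm comparison of post-surgery scores adjusted for the baseline score, either by ANCOVA at each visit or by a repeated-measures mixed model with baseline score, arm, visit and arm-by-visit;
- women analysed by allocated arm, which matters because Section 4.8 allows the device not to be placed after randomisation;
- the adjusted difference with its 95% CI at each post-surgery visit;
- no between-arm test at baseline.

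ANCOVA is enough for the precision point, and the mixed model is a choice. A simple change from baseline is not a substitute. Its variance factor is 2(1 − ρ), which is 1.4 at ρ = 0.3 (worse than ignoring baseline), 1.0 at 0.5 and 0.6 at 0.7, each above the ANCOVA factor.

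Naming one post-surgery visit as the headline comparison is an optional addition that would limit multiplicity.

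The cost is a short edit to Section 6 and slightly more analysis work. No new visits, data or participants are needed.

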7. INDEPENDENT DATA MONITORING COMMITTEE

The study will have an independent committee made up of statisticians, researchers with experience in clinical trials and doctors with expertise in the area of ​​interest. This committee aims to ensure safety for participants throughout the study. Based on data from the collection forms and interim analyses on the effectiveness of the device and safety, the committee will make a recommendation to continue or interrupt the study.

The transition from the first to the second stage of this study is particularly critical and will depend on the recommendation of continuity of this committee and the analysis of a partial (safety) report by the CEP/CONEP System.

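### Interim stopping for benefit is allowed with no efficacy boundary and a flat 5% level, so the overall type I error can exceed the 5% that the trial was sized for

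*Protocol*

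**What the plan says.** Five statements in the protocol bear on this point.

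- **Section 6, looks.** After the look between the two stages, interim analyses are planned "when the casuistry of the second stage reaches 25%, 50% and 75% of the recruitment estimate".
- **Section 6, level.** "In all statistical calculations, the level of significance considered will be 5" per cent. No exception is made for interim analyses.
- **Section 6, test.** Stenosis rates are compared between groups from the 30-day visit onward "using the chi-square test or Fisher's exact test, depending on the values" in the tables.
- **Section 7.** The monitoring committee works from "interim analyses on the effectiveness of the device and safety, the committee will make a recommendation to continue or interrupt the study".
- **Section 4.11.** Among the interruption criteria is "d) the benefit of using the device under interim analysis". No test, p-value or boundary is attached to it.

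Section 5.2 sizes the second stage with "an alpha error of 5%, a beta error of 20% and a balanced allocation 1: 1" and arrives at 120 women per arm. No boundary, alpha spending or adjusted final level appears anywhere in the protocol.

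**The concern.** A trial that may stop early for benefit gives an ineffective device several chances to look effective. If each look and the final test use the full 5%, the chance of at least one false positive is above 5%. The effectiveness claim, which is the primary objective, would then not carry the alpha on which Section 5.2 rests. Once an unadjusted look has been taken, this cannot be credibly repaired.

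**Working it through.** **1. The plan's own sample size.** Inputs from Section 5.2: 15% or 20% against 6%, alpha 5%, power 80%, 1:1 allocation. The two-sided test is inferred, because only that version reproduces the stated figures.

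n' = [1.960·√(2p̄(1−p̄)) + 0.8416·√(p₁(1−p₁)+p₂(1−p₂))]² / (p₁−p₂)²

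With continuity correction: n = (n'/4)·[1+√(1+4/(n'·|p₁−p₂|))]²

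- 15% vs 6%: n' = (0.8497+0.3609)²/0.0081 = 180.9. Corrected, this is 202.6, so 203.
- 20% vs 6%: n' = (0.9322+0.3915)²/0.0196 = 89.4. Corrected, this is 103.2, so 104.

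Both ends of the stated range of 104 to 203 are reproduced by a fixed, single-test design. Nothing in it pays for repeated looks.

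**2. Number of looks.** There are three interim looks plus the final. The look between stages is not counted: the first stage has no control arm, assesses safety only, and its women do not enter the second stage.

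**3. Literal reading, complete data, normal theory.** Under no effect, corr(Z_j, Z_k) = √(t_j/t_k) with t = 0.25, 0.5, 0.75, 1. The probability that |Z| has exceeded 1.96 by looks 1 to 4 is 5.0%, 8.3%, 10.7% and 12.6%, by numerical integration and by simulation.

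**4. Binary data, 30/60/90/120 women per arm, no difference between arms.**

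| Common stenosis rate | Chi-square throughout | Fisher if expected count < 5, else chi-square |
|---|---|---|
| 6% | 11.6% | 7.5% |
| 10.5% | 13.2% | 10.4% |
| 15% | 12.8% | 11.1% |
| 20% | 12.6% | 12.2% |

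The last column is closest to Section 6. The cut-off of 5 is an assumption, since the protocol does not state one.

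**5. Direction.** Section 4.11(d) concerns benefit only. With early stopping only in favour of the device and a two-sided final test (normal theory, complete data), the total error is 8.8%. False claims for the device are 6.3% against a nominal 2.5%, a ratio of 6.3/2.5 ≈ 2.5.

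**6. Outcome delay.** The looks are triggered by recruitment, which Section 5.2 puts at 25 to 30 weeks. Assuming uniform accrual over W weeks and an outcome known L weeks after surgery, the fraction of outcomes available at a look at proportion q is (qW−L)/W, or zero if negative.

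| Outcome tested | Fractions at the three looks (W = 25; W = 30) | Error, normal theory | Error, chi-square/Fisher rule |
|---|---|---|---|
| 30 days (L = 4.3) | 0.08, 0.33, 0.58; 0.11, 0.36, 0.61 | 14-15% | 7.0-11.8% |
| 3 months (L = 13) | 0, 0, 0.23; 0, 0.07, 0.32 | 9-13% | 5.1-9.2% |
| 6 months (L = 26) | 0, 0, 0; 0, 0, 0 | 5% | about 5% |

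In the 30-day row the first look has only about 0.08×120 ≈ 10 to 0.11×120 ≈ 13 women per arm. Normal theory is unreliable there and the last column is the better guide.

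**7. Boundary check.** O'Brien-Fleming limits of 4.049, 2.863, 2.337 and 2.024 at 25/50/75/100% information give a total error of 5.0% by simulation. The matching two-sided p-values are about 0.00005, 0.0042, 0.019 and 0.043.

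**The case against.** **No rule says that p < 0.05 stops the trial.** A reader might infer that the protocol states such a rule. It does not. Section 4.11(d) names no threshold, the committee only recommends, and Section 4.11 requires the ethics committee's opinion before interruption unless risk is imminent. The 5% sentence closes the paragraph on group comparisons, and the looks are described in a separate paragraph. This stands: the 5% threshold at interims is the literal reading, not an explicit instruction.

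**A boundary often sits in a statistical analysis plan or committee charter.** That is true, and a missing boundary alone would not be a finding. But the protocol does not leave the level open. It sets 5% for every calculation, so a later document with adjusted limits would have to contradict it.

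**The error need not be 12-13%.** A reader might take that figure as the trial's actual type I error. The documents do not support this. It requires chi-square tests, complete outcomes at each look and stopping in both directions. The primary objective concerns late stenosis, and hysterometry is first scheduled at 3 months; with an outcome at 6 months or later there is no inflation. This stands as a limit on size. It does not remove the defect: Section 4.10.2 assesses stenosis at every postoperative visit, Section 6 compares rates from 30 days, and no visit is named for the interim test. If only late outcomes counted, 4.11(d) could not operate at these looks.

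**Early stopping exaggerates effects under any boundary.** Correct, so exaggeration is not used here as evidence against the 5% level.

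**Conclusion.** The point holds as a defect in the protocol's own text. Stopping for benefit is permitted, no efficacy boundary is given, the only stated level is 5%, and the sample size assumes one test at 5%. Followed literally, the plan does not guarantee its stated alpha.

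The size depends on what the protocol leaves unnamed: about 5% with an outcome at 6 months or later, about 7.5-12% with complete data under the chi-square/Fisher rule, and up to about 12-13% with chi-square throughout. Benefit-only stopping gives about 8.8% in total.

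These figures assume looks at 30/60/90/120 women per arm or, for delayed outcomes, uniform accrual over 25 to 30 weeks. They assume one tested time point; testing at several visits would add further error that is not counted here. Confidence is high that the level is not protected and lower on the exact excess.

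**What to change.** Amend Section 6 and Section 4.11 in one of two ways.

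1. **Safety-only looks (simpler).** Declare the 25/50/75% looks safety-only, remove 4.11(d), bring the effectiveness wording in Section 7 into line, and test effectiveness once at the end at 5%.
2. **Keep stopping for benefit.** Exempt the interims from the flat 5%. Name the stenosis visit tested and time the looks by the number of women with that outcome. Use an O'Brien-Fleming-type alpha-spending boundary computed at the actual information fractions. Two-sided p of about 0.00005, 0.0042, 0.019 and 0.043 (final) applies only if those fractions are 25/50/75/100%.

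**Cost.** The change is a few lines of text and no more patients. Early stopping for benefit becomes rare or is removed, and under option 2 the final test is slightly stricter. Option 2 also has a practical limit. With a 6-month outcome and uniform accrual, a quarter of outcomes exist only at 0.25×25+26 ≈ 32 weeks to 0.25×30+26 = 33.5 weeks, after recruitment over 25 or 30 weeks has ended. Such a look could not reduce recruitment, which favours option 1 if a late outcome is chosen.
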